**Fig. 1 Fig1:**
[figure not shown]
Research flowchart

General information, medical/treatment history, and pre-assessment results of each participant will be confidentially collected by the research assistant before the initial intervention.

Assessments will be conducted before the intervention (T0), before the 5th intervention (T1), immediately after the 8th intervention (T2), and at the 4th week after the end of the 8th intervention (T3), which include the surface EMG evaluation of pelvic floor muscles, NIH Chronic Prostatitis Symptom Index (NIH-CPSI), three-dimensional quantification, shear wave elastography, and the sympathetic skin response.

The primary outcome measurements will be performed at T0, T1, T2, and T3. Secondary outcome measurements will be carried out at T0 and T3.

The SPIRIT figure is displayed in Table 1.

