### Implementation

The randomization will be done according to the sealedenvelope.com algorithm. The participants will be enrolled after an outpatient visit, and on the following day, the participants will show up for the informed consent. The primary investigator will open the sealed envelope at the end of the baseline examinations.

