### Sample size calculation

Previous studies showed that myofascial release therapy had notable effects [32] (corresponding to a Cohen’s *d* of about 0.5) on improving quality of life, prostate-related symptoms, and pain. The primary outcome will be the change in NIH-CPSI scores, the clinical response rate, and the remission rate as measured by the NIH-CPSI 4 weeks after the completed intervention. We assumed that extracorporeal shockwave combined with myofascial release therapy had similar effects on NIH-CPSI scores. A sample of 40 participants per group was computed by the G*power software to achieve a power of 60% and a level of significance of 5% and a 95% confidence level. To compensate for an estimated dropout rate of 25%, 150 participants will be ultimately required. (i.e., the number in each group is 50).

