### Statistical methods

Statistical analysts perform data analysis in a blind state. All statistics analyses will be performed using SPSS 25.0 for Windows (SPSS Inc., Chicago, IL, USA). All data will be entered into SPSS by the research assistant. A *p*-value of < 0.05 will be considered statistically significant. One-way (3 groups: single extracorporeal shockwave therapy vs single myofascial release therapy vs combined therapy) analysis of variances (ANOVA) with repeated measures will be performed to compare changes in sEMG assessment and NIH-CPSI scores between and within groups over different time points (i.e., T0-T2). A paired sample *t*-test was used to compare the differences in outcome indicators between groups at T2 and T3 to determine the long-term efficacy of each intervention. Post hoc analyses will be performed when any significant difference both between- and within-group is found in any of the outcome variables. Bonferroni correction will be used to adjust the alpha levels. Multilevel regression or a generalized estimating equation (GEE) will also be used as a sensitivity analysis to analyze the correlation between NIH-CPSI scores and the results of sEMG assessment of the pelvic floor muscle and the results of sympathetic skin response. Mediation analysis will examine the mediating effect of sEMG assessment at T1 on the relation between extracorporeal shockwave therapy and NIH-CPSI scores at T2. This study strictly controlled for gender, age, and BMI of the participants, which may affect the primary and secondary outcomes. The mean absolute difference (MAD) and standard error of measurement (SEM) will be used to evaluate inter-method reliabilities. Consequently, Bland–Altman plots will be used to investigate the agreement between NIH-CPSI and SSR. Since the two measurement results have different measurement units, a *Z*-score will be calculated based on the formula: *Z*-score = (observation value − mean value)/SD.

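### The repeated-measures ANOVA treats the pre-treatment T0 value as an outcome and opens arm comparisons on between- and within-group effects: a valid but inefficient test, where T0 as a covariate would cost nothing

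*Protocol article*

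**What the plan says.** The Statistical methods section states that a one-way, three-group "analysis of variances (ANOVA) with repeated measures will be performed to compare changes in sEMG assessment and NIH-CPSI scores between and within groups". It gives the span of visits entered in this model as "over different time points (i.e., T0-T2"). The Study design section fixes what these visits are: "Assessments will be conducted before the intervention (T0), before the 5th intervention (T1), immediately after the 8th intervention (T2"). The Implementation section adds: "The primary investigator will open the sealed envelope at the end of the baseline examinations". T0 is therefore a pre-allocation value, and it enters the ANOVA as one of three outcome levels.

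The condition for comparing arms is: "Post hoc analyses will be performed when any significant difference both between- and within-group is found in any of the outcome variables". On multiplicity, the section states: "Bonferroni correction will be used to adjust the alpha levels".

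The section names neither a group-by-time interaction nor adjustment for the T0 value of the outcome. The multilevel or GEE model is described as relating NIH-CPSI to sEMG and SSR, not as estimating the arm effect. The variables said to be controlled are gender, age and BMI.

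**The concern.** The stated purpose of the ANOVA is to compare changes between arms. Read literally, the two effects that open the pairwise comparisons address that poorly.

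- **Between-group effect.** It compares arm means averaged over T0, T1 and T2. One third of that average is a visit at which randomisation makes the expected difference zero, so the contrast is diluted.
- **Within-group (time) effect.** It asks whether patients change over time, pooled over arms. It is significant when all three arms improve equally, so it says nothing about which treatment is better.

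A real advantage of combined therapy could therefore fail the first condition and never reach a pairwise comparison, while the second condition screens out nothing. The T0 measurement, which could sharpen the comparison, weakens it instead.

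**Working it through.** **The plan's own figure.** The Sample size calculation section uses an effect "corresponding to a Cohen’s *d* of about 0.5", a 5% level, 60% power and 40 per group. A two-sided two-sample t-test (sidedness assumed) with n = 40 per group and d = 0.5 has power 59.8%, so the figure reproduces.

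**Inputs from the article.** Three equal arms, 40 analysed per arm, effect size 0.5 SD, 5% level, visits T0, T1 and T2.

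**Assumed inputs.** Combined arm better than both single arms by 0.5 SD at T2 and by 0.25 or 0.5 SD at T1; unit SD; equal correlation ρ between visits, 0.2 to 0.7.

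**Dilution.** Difference in the T0-T2 average:
- T1 effect 0.25 SD: (0 + 0.25 + 0.5)/3 = 0.25 SD
- T1 effect 0.5 SD: (0 + 0.5 + 0.5)/3 = 0.33 SD

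**Noncentrality.** When one of three arms differs by δ, the squared deviations of the arm means sum to (2/3)δ².
- Between-group: λ = 40 × (2/3)δ² / [(1 + 2ρ)/3], df 2 and 117, with δ the diluted difference.
- Interaction: λ = 40 × (2/3) × Σ(e_t − ē)² / (1 − ρ), df 4 and 234, with e_t the arm difference at visit t.
- ANCOVA of T2 on T0: λ = 40 × (2/3) × 0.5² / (1 − ρ²), df 2 and 116.

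Example with ρ = 0.5 and T1 effect 0.25 SD:
- Between-group: 40 × (2/3) × 0.0625 / 0.667 = 2.50, power 27%
- Interaction: 40 × (2/3) × 0.125 / 0.5 = 6.67, power 51%
- ANCOVA: 40 × (2/3) × 0.25 / 0.75 = 8.89, power 75%

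| T1 effect | ρ | Between-group | Interaction | ANCOVA of T2 |
|---|---|---|---|---|
| 0.25 SD | 0.2 | 37% | 33% | 64% |
| 0.25 SD | 0.3 | 33% | 37% | 67% |
| 0.25 SD | 0.5 | 27% | 51% | 75% |
| 0.25 SD | 0.7 | 23% | 76% | 90% |
| 0.5 SD | 0.2 | 60% | 43% | 64% |
| 0.5 SD | 0.3 | 54% | 49% | 67% |
| 0.5 SD | 0.5 | 45% | 65% | 75% |
| 0.5 SD | 0.7 | 38% | 88% | 90% |

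The between-group test loses power as the visit correlation rises, while ANCOVA gains.

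**Simulation of the two-part condition** (10,000 trials per scenario, common improvement of 0.5 SD at T1 and 1 SD at T2, assumed). The time effect was significant in about 100% of trials, so the condition reduces to the between-group test. It was met in 28% (T1 effect 0.25 SD) and 45% (0.5 SD) of trials at ρ = 0.5, and in 23% and 38% at ρ = 0.7. With no arm difference it was met in 4.7-4.9% of trials; ANCOVA rejected in 5.1-5.2%.

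**The case against.** Several points on the other side stand.

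- **The wording allows other readings.** Comparing changes between groups over time can loosely describe the group-by-time interaction, which does test a difference in change. The interaction is still below ANCOVA in every row of the table, by about 2 to 31 points. If *both* was meant as *either*, no power is lost at the condition, but the time effect opens it almost always and it protects nothing.
- **A reader might infer that the ANOVA tests an unrelated hypothesis or inflates false positives.** It does neither. With no expected difference at T0, the expected difference in the T0-T2 average is two thirds of the mean difference in change over T1 and T2. The test is a diluted but valid version of the right contrast.
- **A reader might infer that the planned 60% power falls to these figures.** The article does not support that. The sample size text ties its outcome to 4 weeks after the intervention, which is T3, and this ANOVA ends at T2.
- **The condition refers to any outcome variable.** If a result on one measure opens comparisons on all of them, it opens more often than these single-outcome figures show.
- **The gain varies.** At ρ = 0.2 with the full effect at T1, ANCOVA adds only about 4 points over the between-group test (64% against 60%).

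The plea that an unseen analysis plan may settle this carries less weight. The article itself fixes the model, the time points and the condition, and a plan that followed them would inherit the weakness.

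**Conclusion.** The point holds as a matter of efficiency and clarity; it should be fixed. Read literally, the plan dilutes a 0.5 SD effect at T2 to 0.25-0.33 SD and has about 23-60% power to open the arm comparisons, against 64-90% for ANCOVA of T2 on T0. On the interaction reading, power is about 33-88%. ANCOVA was best in every scenario tried with ρ from 0.2 to 0.7, but the size of the gain depends on that correlation and on the T1 effect, neither of which the article gives. Type I error is about 5% for the literal test. The size of the loss is confident only as a range, because three readings of the condition remain possible.

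**What to change.** Remove T0 from the outcome vector. For NIH-CPSI and each analysed sEMG measure, use T0 of the same measure as a covariate, in an ANCOVA or in a repeated-measures model with arm, visit, arm-by-visit and T0. Cover the post-baseline visits, including T3, the visit that the sample size names. Base conclusions on the Bonferroni-adjusted arm contrasts from that model, not on between- and within-group main effects.

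Do not simply make the group-by-time interaction the new condition. When the correlation is low and the effect is already full at T1, it has less power than the between-group test: 43% against 60% at ρ = 0.2, and 49% against 54% at ρ = 0.3.

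The cost is a change of analysis wording, best made before unblinding. The article already schedules both primary measures at T0 and at every later visit, so no extra patient, visit or measurement is needed.

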### Sequence generation

Randomization 1:1:1 is done using https://www.sealedenvelope.com/simple-randomiser/v1/lists with varying block randomization with a block size of 6. No stratification is used.

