It is now recommended by the British Urology Association that the main aim of CP/CPPS treatment is to mitigate functional damage to patients [42], usually with single internal and external fascia manipulation. However, most of the studies on myofascial release therapy are pre-and post-controlled trials while lacking high-quality randomized controlled trials [43]. As mentioned in the literature review, myofascial release therapy can effectively alleviate the symptoms of pelvic floor pain in patients, but evidence for the intervention efficacy remains greatly inconclusive because the main primary outcome in existing studies is subjective scale [32, 44, 45]. At present, there are no studies on myofascial release therapy combined with extracorporeal shockwave therapy. Our study will compare three treatments—single myofascial release therapy, extracorporeal shockwave therapy, and combined therapy—and then propose to compare the relationship between the three treatment modalities and the subjective and objective functional changes before and after treatment.

In previous assessments, we found that the symptoms of chronic pelvic pain syndrome may be closely associated with increased pelvic floor muscle tone, which can be effectively reduced with myofascial release therapy. In this study, by comparing the association between the primary and secondary outcome measure and different therapy modalities (extracorporeal shockwave, myofascial release, and combined therapy) on the therapeutic effect of pelvic floor hypertonia at T0-T3 stage, it was proposed to determine (1) if shockwave therapy can reduce pelvic floor muscle tension further after taking myofascial release therapy; (2) if the combined therapy can reduce pelvic floor muscle tone, relieve the discomfort symptoms, and improve the quality of life of the patients more efficiently and have a long-term effect than single treatment [46, 47]; (3) if curative effect can be reflected by the change of sympathetic skin response before and after treatment; and (4) if there exist other mechanisms that may improve the symptoms of patients other than what extracorporeal shockwave and myofascial release therapy did on reducing pelvic floor muscle tone.

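### If Bonferroni is meant for the three arm pairs, it is needlessly conservative for comparing arms on one endpoint at one time point; a closed three-arm test would keep 5% error with more power

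*Protocol article*

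**What the plan says.** The Statistical methods section plans a repeated-measures ANOVA of three groups on sEMG and NIH-CPSI over T0 to T2. It continues: "Post hoc analyses will be performed when any significant difference both between- and within-group is found in any of the outcome variables". The next sentence is "Bonferroni correction will be used to adjust the alpha levels". The text does not say whether the adjustment runs over arm pairs, time pairs, outcomes or a mixture.

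The Sample size calculation section assumes a Cohen's d "of about 0.5) on improving quality of life, prostate-related symptoms, and pain" and states: "A sample of 40 participants per group was computed by the G*power software". The target given there is 60% power at 5% significance. No multiplicity adjustment enters that calculation. The Discussion makes combined against single therapy a central question, asking "if the combined therapy can reduce pelvic floor muscle tone, relieve the discomfort symptoms" and do so better than single treatment.

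**The concern.** With three arms there are three pairwise hypotheses, and any two of them together imply that all three arms are equal. A three-arm omnibus test on the same endpoint already covers that global hypothesis. Once it is significant, at most one true pairwise equality can remain, and one test at 5% cannot exceed 5% error. Dividing alpha by three after that step is valid but stricter than a 5% familywise level requires.

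This matters because the trial is planned at only 60% power, and that figure belongs to an unadjusted comparison. If each arm pair is judged at 0.0167, the contrasts of most interest have clearly less power than the sample size section suggests, and part of the loss is avoidable.

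**Working it through.** **Inputs.** d = 0.5, 40 evaluable per arm, 60% power, 5% significance, 25% dropout and 150 in total (Sample size calculation); equal allocation to three arms (Sequence generation). Assumed: two-sided tests, a normal outcome with common variance, and a Bonferroni family of three arm pairs, so 0.05/3 = 0.0167.

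**1. The plan's own figure.** Normal approximation: n = 2(1.960 + 0.253)²/0.5² = 39.2, so 40 per arm. Exact power uses noncentrality d√(n/2) = 0.5 × √20 = 2.236, which gives 59.8% by the noncentral t. The stated 60% is therefore an unadjusted two-sided two-arm comparison. The total is 3 × 40 × 1.25 = 150.

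**2. Same comparison at 0.05/3.** Power at 40 per arm is 42.1%. Restoring 60% would need about 57–58 per arm.

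**3. Error of the closed procedure.** The omnibus F at 5% is followed, only if significant, by pooled-variance pairwise t tests at 5%. Simulation (400,000 runs, one endpoint, one time point, 40 per arm) gives this familywise error:
- all arms equal: 4.95%
- two equal, third 0.5 SD apart: 4.7%
- two equal, third far apart: 5.0%

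**4. Power, same simulation.** Means are in SD units, combined arm last.

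| Means | n per arm | Criterion | Omnibus, then pairs at 5% | Omnibus, then pairs at 0.05/3 |
|---|---|---|---|---|
| 0 / 0 / 0.5 | 40 | each combined-vs-single contrast | 52.6% | 42.3% |
| 0 / 0 / 0.5 | 40 | both contrasts | 43.3% | 26.4% |
| 0 / 0 / 0.5 | 40 | at least one true difference | 61.9% | 58.2% |
| 0 / 0.25 / 0.5 | 40 | largest contrast | 47.2% | 42.0% |
| 0 / 0.5 / 1.0 | 40 | each adjacent pair | 60.1% | 42.7% |
| 0 / 0 / 0.5 | 50 | each combined-vs-single contrast | 63.7% | 53.0% |
| 0 / 0 / 0.5 | 50 | both contrasts | 54.8% | 36.7% |

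After 25% dropout, 50 × 0.75 = 37.5 per arm remain. At 38 per arm, with means 0 / 0 / 0.5, the figures are about 50% against 40% per contrast and 41% against 24% for both.

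**5. With two co-primary endpoints.** If alpha is split to 0.025 each, the closed procedure gives about 41% per contrast, against about 33% with pairs at 0.025/3.

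**6. What happens if Bonferroni is simply dropped from the plan as written.**
- Another outcome triggers the post hoc tests: error over the three pairs of a null outcome is 12.1%, against 4.3% at 0.05/3.
- A group-by-time test triggers comparisons at T0, T1 and T2 (assumed within-patient correlation 0.5, effect only at T2): 17.6% (d = 0.5) to 24.0% (d = 1), against 7.1% to 9.5% at 0.05/3.
- Two independent null outcomes, each with its own omnibus test at 5%: 1 − 0.95² = 9.75%.

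**The case against.** A reader might infer that, with three arms, the significant overall test already controls the error and Bonferroni buys nothing. The documents do not support that. The planned overall test is not a single comparison of three means: it is a repeated-measures analysis, several outcomes can trigger the follow-up tests, and those tests include within-group comparisons over time. In that setting Bonferroni gives real protection, as step 6 shows.

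Nor is there a double penalty. With means 0 / 0 / 0.5 at 40 per arm, Bonferroni alone gives about 42.6% per contrast, and the overall test plus Bonferroni 42.3%. Almost all of the loss comes from dividing alpha.

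It is also fair to object that 0.05/3 is not in the text. If the intended family is endpoints or time points, the plan already has that part of the correction, and the full protocol may say so. Bonferroni after ANOVA is valid in any case, and the largest gains belong to particular mean patterns.

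All of this stands. It limits the point to one endpoint and one time point and makes it a matter of efficiency. It does not remove it: within that scope the closed procedure rejects everything that the overall test plus Bonferroni rejects, and more, at the same 5% familywise level.

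**Conclusion.** The point holds in a limited form. For the between-arm comparison of one named endpoint at one named time point, and if Bonferroni is meant over the three arm pairs, the plan gives up power that a 5% familywise level does not require. At 40 per arm, with combined therapy 0.5 SD better than two equal single arms, the cost is about 10 points per contrast and 17 points for winning both. It is about 5 points for the largest contrast when means are evenly spaced up to 0.5 SD, and 3–4 points for finding any true difference. With two co-primary endpoints it is about 8 points per contrast.

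Separately, the stated 60% power does not describe a Bonferroni-adjusted pairwise comparison, which has about 42%.

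The plan's error control is not at fault here, and the result gives no licence to delete Bonferroni from the current text.

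**What to change.** Rewrite the multiplicity sentences in Statistical methods to do the following:

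1. Name one endpoint and one time point for the main between-arm comparison, for example change in NIH-CPSI score 4 weeks after treatment, which the Sample size calculation section already uses. That is T3, and the planned ANOVA covers only T0 to T2, so a three-arm test at T3 must be added.
2. Test the three arms on that endpoint with one omnibus test at 5%. Only if that same test is significant, test the three pairs at 5% each without Bonferroni (Fisher's protected LSD, which is closed for exactly three arms).
3. Keep a stated correction across endpoints, across time points and for within-group time comparisons. If sEMG and NIH-CPSI both stay primary, divide alpha between them first and run the procedure within each share.
4. State the power for the pairwise contrasts under the rule finally adopted.

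The cost is a short rewrite and no extra patients. The drawback is that the pairwise 95% intervals are no longer simultaneous, which the text should say. If the sponsor prefers to keep Bonferroni over the arm pairs, the plan should name that family and report the power of about 42% at 40 per arm.

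### The mediation analysis names no baseline adjustment, so if shockwave changes sEMG at T1, a stable link between muscle tone and symptoms can appear as mediation

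*Protocol article*

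**What the plan says.** The mediation analysis has one sentence in the protocol article, under Statistical methods: "Mediation analysis will examine the mediating effect of sEMG assessment at T1 on the relation between extracorporeal shockwave therapy and NIH-CPSI scores at T2". It fixes the exposure, the visit of the mediator and the visit of the outcome. It names no covariate and no change score. By contrast, the repeated-measures ANOVA in the same section is meant "to compare changes in sEMG assessment and NIH-CPSI scores between and within groups over different time points (i.e., T0-T2"), so T0 enters that analysis.

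The T0 values exist. Study design says: "The primary outcome measurements will be performed at T0, T1, T2, and T3", and sEMG and NIH-CPSI are the primary measures.

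On how the two measures relate, the Discussion says that "the symptoms of chronic pelvic pain syndrome may be closely associated with increased pelvic floor muscle tone". It gives no correlation. The fourth question listed there asks whether anything other than reduced muscle tone explains improvement, and the mediation analysis bears directly on it.

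Statistical methods also says: "This study strictly controlled for gender, age, and BMI of the participants, which may affect the primary and secondary outcomes". This sentence is not tied to the mediation model.

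**The concern.** An indirect effect is the product of two paths: a, from shockwave to T1 sEMG, and b, from T1 sEMG to T2 NIH-CPSI within arm. Randomisation makes a a fair comparison. It does nothing for b, because nobody is randomised to a level of muscle tone.

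If patients with high tone also tend to have more symptoms, and both features persist, those patients will have high sEMG at T1 and high NIH-CPSI at T2 whatever tone does to symptoms. Path b is then non-zero for a reason that is not mediation. Once shockwave also shifts T1 sEMG, the product a × b is non-zero and is read as benefit passing through muscle tone.

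At stake is the trial's answer on mechanism. The error would appear exactly when shockwave does lower sEMG, which the trial hopes to show. It is bias rather than noise, so more patients make it more likely to reach significance.

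**Working it through.** **Inputs from the protocol article**
- Mediator sEMG at T1, outcome NIH-CPSI at T2 (Statistical methods).
- 40 evaluable and 50 randomised per group, power 60%, alpha 5%, standardised effect 0.5 (Sample size calculation).
- 1:1:1 allocation; "No stratification is used" (Sequence generation).

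**Inputs that are assumed, because the article gives none**
- A two-arm contrast for shockwave, since the article does not say which arms form it.
- Shockwave effect on T1 sEMG: a = -0.5 SD, varied from 0 to -0.8.
- Tone-symptom correlation ρ from 0 to 0.7.
- Persistence of each measure 0.7.
- True effect of sEMG on NIH-CPSI zero, so true mediation is zero.

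**Step 1: the plan's own figure.** For d = 0.5, two-sided alpha 5% and power 60%, the two-sample formula gives 40 per group. Power at 40 is 0.609 by the normal approximation and 0.598 by the noncentral t. The figure reproduces. It also gives the chance, about 0.60, that path a is significant when a = -0.5 SD.

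**Step 2: size of the spurious path b without T0 (all variances 1)**
- Model 1: each follow-up value is 0.7 times its T0 value, plus treatment, plus independent error; ρ is the T0 correlation. Then b = 0.7 × 0.7 × ρ = 0.49ρ.
- Model 2: each measure is a stable patient trait carrying 70% of its variance, plus independent error; ρ is the trait correlation. Then b = 0.7ρ.

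| Model | ρ | b | a × b at a = -0.5 |
|---|---|---|---|
| 1 | 0.3 | 0.147 | -0.07 SD |
| 1 | 0.5 | 0.245 | -0.12 SD |
| 2 | 0.3 | 0.210 | -0.11 SD |
| 2 | 0.5 | 0.350 | -0.18 SD |

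The true value is 0 in every row.

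**Step 3: chance of declaring mediation.** Mediation is declared when both paths have p < 0.05. With 80 patients, t for path b is about b√77 / √(1 - b²), and the joint rate is about 0.60 times the power of path b.
- b = 0.147: t = 1.30, power 0.26, joint rate 0.60 × 0.26 = 15%.
- b = 0.245: t = 2.22, power 0.60, joint rate 36%.
- b = 0.210: t = 1.89, power 0.47, joint rate 28%.
- b = 0.350: t = 3.28, power 0.91, joint rate 54%.

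Simulation with 2,000 to 3,000 data sets per scenario agrees:

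| Model, 40 per arm, a = -0.5 | Without T0 | With T0 sEMG and T0 NIH-CPSI |
|---|---|---|
| 1, ρ = 0.3 | 16% | 4% |
| 1, ρ = 0.5 | 36% | 4% |
| 2, ρ = 0.3 | 28% | 6% |
| 2, ρ = 0.5 | 54% | 9% |
| 2, ρ = 0.7 | 61% | 17% |

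**Step 4: when there is no problem.** With ρ = 0 the rate is about 3-5% with or without T0. With a = 0 and no T0 values it is 2%, 4% and 6% at ρ = 0.3, 0.5 and 0.7 in model 2, and the mean indirect effect is about zero. Path a then rejects only at its 5% level, so the 6% is simulation error around that ceiling.

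**Step 5: sensitivity (model 2, ρ = 0.5, no T0).** At 40 per arm: a = -0.3, 25%; a = -0.8, 84%. At 50 per arm: a = -0.3, 31%; a = -0.5, 67%. At 40 per arm and a = -0.5, a stable share of 0.5 or 0.9 gives 38% or 60%.

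**Step 6: why T0 adjustment may leave something.** In model 1 the observed T0 values carry all the confounding, so adjusting removes it. In model 2 they measure the trait with error. At ρ = 0.5 the adjusted b is 0.036 / 0.497 = 0.07, so a × b = -0.04 SD remains, against -0.18 SD unadjusted.

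**The case against.** **The article is silent; it does not exclude T0.** This is the strongest objection. A reader might infer that the sponsor has decided to omit baseline values. The text does not say so, and a covariate list may sit in a document not shown. What stands is narrower: the sentence fixes the visits of mediator and outcome and names no T0 value, and run as written it does not separate mediation from a stable association.

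**The sentence on gender, age and BMI may look like the adjustment set.** It is weak evidence for that. Eligibility criteria admit only men aged 20-40 and exclude BMI above 22.9, so the sentence reads as control by restriction. Gender is constant and could not be a covariate. The point does not rest on it.

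**A stable link alone does not create mediation.** This is correct. Path a is randomised, and without a shockwave effect on T1 sEMG the false-positive rate stays near or below 5%. The condition is part of the point.

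**The inputs are not the protocol's.** This is also correct. The effect "corresponding to a Cohen’s *d* of about 0.5" is for myofascial release on quality of life, symptoms and pain, not for shockwave on sEMG. T1 falls before the fifth of eight sessions, and the comparison arm may receive release, which the Discussion credits with lowering tone. The effect on T1 sEMG could therefore be small. The Discussion's association is tentative, has no size, and is not said to hold before treatment.

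**The analysis is subsidiary.** None of the three aims listed in the Background names sEMG mediation.

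**Conclusion.** The point holds in conditional form. As written, the analysis leaves the path from sEMG to NIH-CPSI open to confounding by stable patient differences of a kind the Discussion itself expects. If shockwave changes T1 sEMG relative to the comparison arm, mediation can be declared when there is none. The rate is about 16-54% without T0 values and about 4-9% with them, for 40 per arm, a 0.5 SD effect on sEMG, a T0 or trait correlation of 0.3 to 0.5 and persistence of 0.7. All of these except the 40 per arm are assumptions for this analysis. The direction is the same under both data models; the size is not known.

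Two stronger readings are not supported. One is that the analysis will often credit muscle tone wrongly: that depends on a correlation and an sEMG effect that the article does not give. The other is that T0 adjustment fully cures the problem: under the stable-trait model the rate remains 17% at ρ = 0.7.

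This is a free improvement to an explanatory analysis. The comparisons between treatment groups are unaffected.

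**What to change.** Extend the mediation sentence under Statistical methods to say three things:
1. T0 sEMG and T0 NIH-CPSI are covariates in both the mediator model (sEMG at T1) and the outcome model (NIH-CPSI at T2).
2. The indirect effect is estimated from these adjusted models and reported with a bootstrap confidence interval.
3. T0 adjustment greatly reduces confounding of the path from sEMG to NIH-CPSI but may not remove it, so the result is exploratory.

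The cost is wording only. Both T0 values are already collected, and no visit, measurement or patient is added.
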